### Secondary outcomes

Levels of participant retention and data compliance will be measured by loss to follow-up, missing data and withdrawal at the end of the trial will be collected. Data will be collected on outcomes that we plan to collect in the definitive trial. While this feasibility trial is underpowered to detect meaningful differences, an attempt can be made to ensure all the relevant data are able to be collected. Further, the current favoured outcome measure for the full RCT trial, PROMIS [16], can be assessed as an effective primary outcome and used in the power calculations for the definitive trial.

The following clinical scores will be collected; Oxford Shoulder Score (OSS) [17], Pain visual analogue score (VAS), EQ-5D-5L score [18], Work Productivity Impairment Questionnaire (WPAI) [19] and patient/hospital reported resource use including referral rates for shoulder surgery at baseline, 3 months and 6 months. We will gather data on any complications of either intervention at 6 months.

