### Statistical considerations and data analysis

Fifty participants will be recruited for this feasibility study. This sample size will be sufficient to estimate the rate of recruitment (i.e., participants randomised out of those screened) and retention.

Fifty participants should provide a robust estimate of the standard deviation around the PROMIS upper limb physical function to be used in the sample size calculation for a definitive trial. Specifically, to prepare for a definitive trial with an anticipated small standardised difference (0.1–0.3) and 80% power, a pilot study sample size of 40 participants (20 per arm) would be sufficient to estimate reliable input parameters for the sample size estimation of the definitive trial [20]; 50 participants will allow for up to 20% loss to follow-up.

The data analysis will be mainly descriptive for the feasibility trial, focussing on the primary outcome, i.e. the conversion rate of eligible to randomised participants, and the total number of participants recruited, as well as on retention and compliance data. Data on patient-reported outcomes, adverse events and complications will also be presented.

Descriptive statistics will be presented for all patient-reported outcomes at baseline and follow-up. Complications and adverse events/serious adverse events reported during the trial follow-up will also be summarised. Data will be presented by the treatment arm and overall. Mean and standard deviation (or median and interquartile range if non-normally distributed) for continuous variables and the number and percentage of participants in each group for binary or categorical variables will be presented.

Differences in outcomes between treatment arms at the follow-up time points will be presented as mean differences with corresponding 90% confidence intervals for continuous data, and risk differences and odds ratios with 90% confidence intervals for binary data, where appropriate. If sufficient outcome data are available, differences will be adjusted for the duration of symptoms (< = / > 6 months) and baseline scores for continuous variables, where applicable, and derived from multilevel mixed-effects linear or logistic regression models. If insufficient data are available, unadjusted differences will be presented.

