Summaries by treatment arm will be based on the intention to treat (ITT) population. The ITT population will include all participants with available data for at least one of the follow-up timepoints up to and including 6 months follow-up in the randomised groups to which they were allocated regardless of the treatment they received.

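### The set called intention to treat admits only participants with some follow-up data, so by-arm retention can be overstated and by-arm baseline and safety summaries become selected

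*Protocol article*

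**What the plan says.** The closing paragraph of the protocol article's section on statistical considerations and data analysis states: "Summaries by treatment arm will be based on the intention to treat (ITT) population". It then sets the rule for entry to that population: "The ITT population will include all participants with available data for at least one of the follow-up timepoints". The last timepoint that counts is 6 months, and members are kept in their allocated arm whichever injection they had. The article names no all-randomised population and no separate safety population.

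Earlier in the same section, the descriptive analysis is said to focus on the conversion rate, the number recruited, and retention and compliance. Patient-reported outcomes at baseline and follow-up, complications and adverse events are also to be summarised, and results are to be shown per arm and for both arms combined. Under Secondary outcomes: "Levels of participant retention and data compliance will be measured by loss to follow-up, missing data and withdrawal". Under Aims and objectives, recruitment rates and participant retention are the uncertainties named as needing an answer before a large trial.

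**The concern.** The definition has two parts, and only one of them is intention to treat. Analysing people in their allocated arm whatever they received is. Requiring at least one follow-up record is not, because membership then depends on a post-randomisation event. The as-allocated clause does not bring back those whom the data requirement removes.

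For most trials this would be mainly a labelling fault. Here retention is itself an outcome. If by-arm retention is calculated in this set, a participant must have been retained to some degree in order to be counted, and complete losses vanish from the denominator. The result can err in one direction only. It also narrows or removes a difference in disengagement between arms, which is useful to know when planning the definitive trial.

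By-arm baseline tables would describe responders rather than the randomised groups. For safety, the article has site staff recording events and carrying out a medical notes review at 6 months, so an event can be known for someone who returned no questionnaire. Unless such site records count as follow-up data, which the text does not say, that person and that event drop out of the by-arm complication and adverse event tables.

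**Working it through.** **Inputs from the protocol article (statistical considerations).** Planned number: "Fifty participants will be recruited for this feasibility study". Number needed: "a pilot study sample size of 40 participants (20 per arm) would be sufficient". Allowance for loss: "50 participants will allow for up to 20% loss to follow-up". Allocation is 1:1 (Randomisation and blinding), so about 25 per arm.

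**The plan's own figure.** 40 / (1 − 0.20) = 50. The sample size reproduces exactly. The allowance amounts to 50 − 40 = 10 participants lost.

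**Assumption.** The article does not say how many of those lost would have no follow-up data at all. Call this number k and let it run from 0 to 10.

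**Overall size of the distortion.** Retention among all randomised is 40/50 = 80% (exact 95% interval 66% to 90%). On the article's denominator it is 40 / (50 − k). Both arms are pooled here only to show the scale, since the rule itself governs by-arm summaries.

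| k (never respond) | Denominator | Retention | Overstatement |
|---|---|---|---|
| 0 | 50 | 80.0% | 0 points |
| 2 | 48 | 83.3% | 3.3 points |
| 5 | 45 | 88.9% | 8.9 points |
| 10 | 40 | 100% | 20 points |

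**Contrast between arms.** As an illustration with the same 40 retained, take 22/25 = 88% against 18/25 = 72%, a gap of 16 points. The losses are 3 and 7.

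- None of those lost is a never-responder: 88% against 72%, no distortion.
- Half never respond (1.5 and 3.5 on average): 22/23.5 = 93.6% against 18/21.5 = 83.7%, a gap of about 10 points.
- All never respond: 22/22 against 18/18, both 100%, no gap.

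**Safety.** Suppose an arm of 25 has 20 participants in the set, 2 of them with an event: 2/20 = 10%. The 5 excluded participants decide the direction:

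- No events among them: 2/25 = 8%, so the article's set gives too high a rate.
- One event: 3/25 = 12%, so it gives too low a rate.
- Two events: 4/25 = 16%, so it is lower still than the full rate.

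Baseline summaries behave likewise. They are selected, but the direction depends on who fails to respond.

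**What does not use the set.** The primary outcome is conversion from eligible to randomised. The progression criterion is recruitment of 50. Neither needs follow-up data. The restriction is worded for summaries by arm, so overall retention is not bound by it.

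**The case against.** The best defence is that nobody would calculate retention this way. The article justifies 50 participants as enough to estimate retention and speaks of loss as a share of those 50, so its implied denominator is everyone recruited. Loss to follow-up and withdrawal mean little in a set that excludes complete losses. Nor is retention explicitly said to be reported by arm: it is listed beside the conversion rate, which cannot be split by arm, and the sentence on by-arm presentation follows the patient-reported outcomes and adverse events. On this view the definition was meant for outcome summaries and is merely worded too broadly. For those outcomes, people with some follow-up data analysed as allocated is a reasonable set.

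Much of this stands. It makes the point one of wording that needs correcting, and it is no evidence of what the final report will show. But the rule covers by-arm summaries without exception, and no other population is offered for retention, baseline or safety.

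The size also depends on what counts as a follow-up timepoint. Participants are contacted weekly to week 8, adverse events are sought at 8 weeks, and questionnaires follow at 3 and 6 months. If one weekly reply suffices, few may be excluded; if the notes review counts, perhaps none. The text does not settle this.

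A reader might infer that all the by-arm summaries are biased upward. The documents support that for retention only. A reader might also infer that the trial will report 100% retention, or that differential loss will be wholly hidden. That requires every lost participant to have returned nothing.

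**Conclusion.** The point holds in a limited form. The set is mislabelled, and followed literally it can only overstate by-arm retention. It makes by-arm baseline and safety summaries selected, with no determinate direction of bias. With the article's own 20% allowance, the overstatement of retention lies between 0 and 20 percentage points, depending on an unstated number of never-responders. In the illustrative contrast, a 16-point gap between arms shrinks to about 10 points if half of those lost never respond, and disappears only at the extreme.

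It would be wrong to conclude that the feasibility decision is compromised. The primary outcome and the progression criterion do not use this set, and the by-arm comparisons are descriptive and acknowledged to be underpowered. The definition should be corrected, because retention is a stated aim and the protocol itself fixes the rule, but the fault does not undermine the trial.

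**What to change.** Define the intention-to-treat population as all randomised participants in their allocated arm. Use it as the denominator for by-arm retention, withdrawal, data compliance, baseline characteristics, and complications and adverse events.

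Rename the present set the available-case set and use it only for differences in patient-reported outcomes. State whether the weekly contacts and the 6-month notes review count as follow-up timepoints for entry to it. For each such analysis, report the number contributing out of the number randomised, by arm.

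This costs a short change of wording and needs no further data. The only drawback is that by-arm retention may look less favourable.

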#### The APS intervention

After the consent and randomisation processes, a 55-ml sample of blood will be obtained and taken to the sample preparation area. The blood will be used for the preparation of the APS injection. The solution will be created as per the manufacturer’s guidelines. It is a two-step process taking 15–20 min—firstly, the blood is separated by centrifuging it, after which it is concentrated in specialised tubes. The total volume of the resultant APS is approximately 3 mls, and does not contain any local anaesthetic. This solution will be delivered in an identical manner to the control treatment but provided in a ‘blinding syringe’ (non-transparent sides).

The APS injection kit is manufactured on behalf of Zimmer Biomet, a medical device manufacturer, it has the trade name of nSTRIDE. nSTRIDE is fully licenced for use in the UK, and the processing machines have the appropriate CE markings.

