### Data collection

At baseline demographic data, patient function and pain data using the PROMIS physical function, PROMIS Pain interference, Oxford Shoulder Score, VAS and Work Productivity Impairment questionnaires will be collected after the participant has provided consent. Participants will also be asked to complete the EQ-5D-5L health-related quality-of-life questionnaire to indicate their typical health status. All case report forms (CRFs) including screening, consent, randomisation and baseline assessment will be completed online on the REDCap database.

Data collection will be divided into two phases, early and late phase follow-up:*Early*—participants will receive a weekly text/email/phone call (according to participant preference) up to week 8 post-randomisation with a link to a visual analogue scale (VAS) asking them to indicate their level of pain in the previous 24 h and whether during that week if they have taken any painkillers for their injury.*Late*—at 3 and 6 months post-randomisation, participants will be contacted by the Oxford central study office via automated SMS or email from the REDCap database and invited to complete the PROMIS, OSS, EQ-5D-5L, VAS, WPAI, health resource use and complications questionnaires.

Complication data will be collected from patients at 3 and 6 months post-randomisation. Complications will be patient-reported via their 3- and 6-month questionnaires and verified by research nurses at the site. At 6 months post-randomisation the site staff will be asked to complete a medical notes review to ensure all expected complications are recorded.

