### Trial oversight and management

The Trial Management Group (TMG), which includes a patient member will meet regularly, at least once a month, to ensure successful delivery of the trial. The TMG will monitor the rate of recruitment, any departure from the protocol or other safety concerns.

The trial statistician and the information specialist will be closely involved in setting up data capture systems, design of databases and clinical reporting forms. As this is a low-risk, small feasibility study no Trial Steering or Data and Safety Monitoring Committee will be convened.

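### Minor: by-arm safety summaries follow allocation only, so a complication after an index-injection deviation is counted against an injection the person did not have

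*Protocol article*

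**What the plan says.** Three statements in the Protocol article, under Statistical considerations and data analysis, combine into one rule.

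- Safety data are tabulated: "Complications and adverse events/serious adverse events reported during the trial follow-up will also be summarised".
- The layout is by arm: "Data will be presented by the treatment arm and overall".
- The closing paragraph fixes the analysis set, "Summaries by treatment arm will be based on the intention to treat (ITT) population", and groups its members "in the randomised groups to which they were allocated regardless of the treatment they received".

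No other grouping is named for safety. The overall column pools the two injections, so it cannot separate them.

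The order of events is set under The APS intervention: "After the consent and randomisation processes, a 55-ml sample of blood will be obtained and taken to the sample preparation area". Allocation is therefore fixed before anyone knows whether the blood draw and the two-step preparation will succeed.

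**The concern.** Several of the foreseeable complications listed under Serious adverse events depend on what was injected, for example fat atrophy, skin pigmentation and pain flare at the injection site. If an APS-allocated participant is given CSI because the draw or the preparation fails, and then has one of these, the planned table puts the event in the APS row. If a participant in either arm leaves uninjected, that person stays in the denominator of an injection never given and dilutes its rate.

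What is at stake is how the table is read. A team planning the definitive trial will want to know what follows each injection, and a table by allocation answers that only when everyone received what was allocated. The point concerns the index injection alone. It does not concern treatment given after the referral at 6 to 8 weeks.

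**Working it through.** **The plan's own figure.** The article needs 40 evaluable participants (20 per arm) and states that "50 participants will allow for up to 20% loss to follow-up". Check: 40 / (1 − 0.20) = 50, which reproduces. With 1:1 allocation an arm has 50 / 2 = 25 participants, or 20 after the allowed loss. The point does not depend on this figure beyond setting the row size n.

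**Inputs.** n = 25 or 20 comes from the article. The article gives no deviation rate and no complication rate, so the following are assumptions:

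- k = 1 to 3 deviations in an arm
- event rate after APS 10%
- event rate after CSI 20%
- event rate with no injection b = 0% to 5%

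**Expected row rate under the planned table.**

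- APS row, k given CSI: [0.10(n − k) + 0.20k] / n
- APS row, k uninjected: [0.10(n − k) + bk] / n
- CSI row, k uninjected: [0.20(n − k) + bk] / n

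For example, with n = 25 and k = 3 given CSI: (0.10 × 22 + 0.20 × 3) / 25 = 2.8 / 25 = 11.2%. With n = 20 and k = 3 uninjected in the CSI row at b = 0: (0.20 × 17) / 20 = 3.4 / 20 = 17.0%.

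| Row and deviation | n | k = 1 | k = 3 |
|---|---|---|---|
| APS (10%), given CSI | 25 | 10.4% | 11.2% |
| APS (10%), given CSI | 20 | 10.5% | 11.5% |
| APS (10%), uninjected, b = 0 / 5% | 25 | 9.6% / 9.8% | 8.8% / 9.4% |
| APS (10%), uninjected, b = 0 / 5% | 20 | 9.5% / 9.75% | 8.5% / 9.25% |
| CSI (20%), uninjected, b = 0 / 5% | 25 | 19.2% / 19.4% | 17.6% / 18.2% |
| CSI (20%), uninjected, b = 0 / 5% | 20 | 19.0% / 19.25% | 17.0% / 17.75% |

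The shifts run from 0.2 points (10% to 9.8%) to 3.0 points (20% to 17.0%).

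**Against sampling error.** At 10%: √(0.09/25) = 6.0 points and √(0.09/20) = 6.7 points. At 20%: √(0.16/25) = 8.0 points and √(0.16/20) = 8.9 points. Every expected shift is below the standard error of its row.

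**One actual event.** A single misplaced event moves a row by 1/25 = 4 points or 1/20 = 5 points. This needs a deviation and an event in the same person. With k APS-allocated participants given CSI, the chance of at least one such event is 1 − (1 − r)^k. At r = 20% this is 20.0% (k = 1) to 48.8% (k = 3). At r = 10% it is 10.0% to 27.1%.

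**A wider assumed gap.** With rates of 10% (APS) and 30% (CSI) and 25 per arm, the difference by injection received is −20.0 points. By allocation it is −19.2 with one APS-allocated participant given CSI (10.8% − 30%) and −17.6 with three (12.4% − 30%). With equal rates, or with no deviations, the two tables have the same expected rates.

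**The case against.** The strongest case against is that a table by allocated arm is legitimate and correctly labelled. A journal article commonly leaves an as-treated safety set to the analysis plan, which is not shown here. Nothing in the article forbids an extra table, and deviations should be known case by case because "The TMG will monitor the rate of recruitment, any departure from the protocol or other safety concerns". With 50 people and one index injection each, any deviation could be footnoted in the report.

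Much of this stands. The as-randomised table should stay, and an unseen plan may already add the other one. What does not stand is that the article is merely silent. It states a grouping rule for by-arm summaries, says the rule holds whatever was received, and has already put safety data in those summaries. Knowing of a deviation does not change the table the rule produces.

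Three stronger readings are tempting, and the article does not support them.

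- A reader might infer that the fourth aim, on complications of either intervention, goes unmet. That aim is worded as gathering data, and the questionnaires, nurse verification and notes review under Data collection serve it.
- A reader might picture crossovers in both directions. A CSI-allocated participant receiving APS is implausible, because the article says control blood is discarded. The credible routes are APS to CSI, APS to none and CSI to none.
- A reader might take the allocation-based table for an error. It keeps the randomised comparison. It simply answers a different question once someone deviates.

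**Conclusion.** The point holds as a minor, cheap improvement. The stated rule can count an injection-specific complication against an injection the person did not have, and the sequence of randomisation before APS preparation makes that possible.

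The size is zero without deviations and small with them: 4 to 5 points for one misplaced event, and less than a standard error in expectation under the assumed rates. Those deviation and event rates are illustrative, since the article gives neither. The eligible-to-randomised conversion, the sample size of 50 and the progression rule do not change, and no decision in this feasibility study turns on the point. The value lies in what the safety data can tell the team designing the definitive trial.

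**What to change.** Keep the as-randomised safety table. Add one sentence to the closing paragraph of Statistical considerations and data analysis, along these lines: *Complications, adverse events and serious adverse events will also be summarised descriptively by the index injection actually received (APS or CSI), among injected participants with safety information; the number with such information will be given, and uninjected participants will be listed separately.* Patient-reported outcomes stay in allocated groups.

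Safety information would come from the questionnaires and from the review already planned: "At 6 months post-randomisation the site staff will be asked to complete a medical notes review to ensure all expected complications are recorded". Giving the count with information keeps injected people without any from being read as event-free.

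The cost is one sentence, one grouping variable and one count. Post-injection follow-up already has site teams able to establish which injection was given. The downside is that denominators may differ between the safety and outcome tables. At 25 per arm, one to three APS-allocated participants given CSI would make the safety denominators 24 and 26 to 22 and 28, before allowing for missing safety information. A footnote should explain the difference.

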### Trial oversight and management

The Trial Management Group (TMG), which includes a patient member will meet regularly, at least once a month, to ensure successful delivery of the trial. The TMG will monitor the rate of recruitment, any departure from the protocol or other safety concerns.

The trial statistician and the information specialist will be closely involved in setting up data capture systems, design of databases and clinical reporting forms. As this is a low-risk, small feasibility study no Trial Steering or Data and Safety Monitoring Committee will be convened.

